# Flexibility and resistance exercises versus usual care for improving pain and function after distal radius fracture in adults aged 50 years or over: protocol for the WISE randomised multicentre feasibility trial

**DOI:** 10.1186/s40814-022-01011-5

**Published:** 2022-03-07

**Keywords:** Distal radius fracture, Pain, Function, Exercise, Adherence, Quality of life

## Abstract

**Background:**

Distal radius fractures represent about 1 in 5 of all fractures treated in UK hospitals. Most distal radius fractures occur in women aged 50 years or over after a fall. Distal radius fractures are managed using splints or casting, some are also treated with surgical fixation. Patients often experience long-term muscle weakness of the hand and arm that may impact their ability to do daily activities such as personal hygiene, routine household chores and food preparation. We propose a structured and tailored flexibility and resistance exercise programme for the hand and arm supplemented with behaviour change strategies to help perform daily exercise. The main aim of our study is to assess the feasibility of conducting a definitive randomised controlled trial.

**Methods:**

This study is a multicentre, parallel-group individually randomised feasibility trial. We will recruit a minimum of 72 adults aged 50 years or over with distal radius fracture treated surgically or non-surgically from at least three UK National Health Service (NHS) hospitals. They will be randomised 1:1:1 to receive usual care, usual care and independent exercise with a single therapy session or usual care and supervised exercise with three therapy sessions over 12 weeks. Our primary feasibility objectives are (1) patient engagement assessed by recruitment, (2) acceptability of the interventions assessed by adherence and patient and clinician experience and (3) retention of participants in the trial. Outcome measures will be assessed at baseline, 3 months and at 6 months after randomisation. A qualitative sub-study will explore the experiences of the trial participants and therapists delivering the exercises.

**Discussion:**

A definitive trial will be considered feasible without major modifications if our progression criteria are met. If successful, the findings will inform the design of a future definitive RCT to evaluate the clinical and cost-effectiveness of the WISE exercise programme.

**Trial registration:**

ISRCTN12290145.

## Background

There are 100,000 distal radius fractures a year in the UK, representing 18% of all fractures seen in hospitals [1]. Most distal radius fractures occur in women aged 50 years or over [2] after reaching out a hand as a protective response to a fall [3]. Initial fracture management is by non-surgical management using splints or casting or, for more complicated fractures, by surgical fixation followed by splints or casting.

Immediately after initial treatment of the fracture, when the cast or splint is removed, the vast majority of patients experience pain and stiffness in their wrist and have muscle weakness of the upper limb, making self-care and activities of daily living difficult [4]. Exercises are often prescribed to improve recovery after distal radius fracture [5]. A recent systematic review, focussing on prescribed exercise after distal radius fracture, found that across nine trials there was insufficient evidence to (i) support referral for therapy, (ii) support patients with exercise progression and (iii) support the use of specific types of exercise, such as resistance training [6].

Current guidance for rehabilitation, in the absence of evidence, reflects common practice in the UK, which is advice from a surgeon or a physiotherapist on self-management [7]. The advice usually includes basic upper limb mobilising exercises to help recover joint range of motion, and provision of a patient information leaflet. Referral to physiotherapy or specialist hand therapy for supervised rehabilitation and specialist splinting is variable and often reserved for the minority of patients who experience serious complications [7].

Current exercise advice focuses on joint flexibility and on graded increase in use of the hand in day-to-day activities. We hypothesise that introducing structured, self-managed resistance exercise training has the potential to improve functional recovery by optimising recovery of muscle strength of the hand and upper limb. In the WISE feasibility trial (Wrist Injury Strengthening Exercise), we propose two different modes of delivering structured flexibility and resistance exercises (independent and supervised) with behaviour change strategies to support self-management. The primary objectives of this study are to determine the feasibility of conducting a definitive, multicentre RCT of structured flexibility and resistance exercise compared to usual care, in improving pain and function after distal radius fractures in adults aged 50 years and over.

## Methods/design

### Trial design

WISE is a multicentre, parallel, 3-group, 1:1:1, feasibility randomised controlled trial assessing two different modes of structured flexibility and resistance exercises versus usual care after distal radius fracture. The study flowchart is presented in Fig. 1. A schedule of enrolment, interventions, and assessments is presented in Fig. 2.

**Fig. 1 Fig1:**
[figure not shown]
Study flow diagram

**Fig. 2 Fig2:**
[figure not shown]
The schedule of enrolment, interventions, and assessments for the WISE trial

### Study setting

Screening, recruitment and intervention delivery will occur in at least 3 National Health Service (NHS) hospitals in the UK over a 6-month period.

### Eligibility criteria

Participants will be included if they are aged 50 years or over with a distal radius fracture treated surgically or non-surgically and willing and able to give informed consent to participate in the trial. Exclusion criteria are if the injury is more than 2 months old or there is evidence that the patient would be unable to participate in therapy appointments or the self-guided exercise programme or adhere to trial procedures (including cognitive impairment and fracture/surgery complications such as Complex Regional Pain Syndrome) or have open fractures with a Gustilo and Anderson grading > 1.

### Recruitment

Potentially eligible patient participants will be identified in the emergency department/minor injuries unit or via virtual or outpatient trauma and orthopaedic services (fracture clinic) and provided with a Patient Information Sheet. Patients that are happy to be approached about participation in the study will either be approached in the clinical setting or via telephone or video call to discuss the trial.

Screening logs recording the age, gender and initial fracture management (surgical or non-surgical), and if provided, the reasons for declining participation will be kept at each site to determine the number of patients assessed for eligibility and reasons for exclusion.

### Consent

Prior to any study-related procedures or data being collected, an online informed consent form will be completed. Permission from the participants will also be obtained to inform their general practitioner of their inclusion in the study. The person who obtains the consent will be suitably qualified and experienced and have been delegated to do so by the Chief/Principal Investigator.

After an informed consent discussion either in person or via telephone/video call, those happy to participate will provide their consent using the latest approved version of the online Informed Consent Form. If the contact is not in person and the participant does not have internet access, the consent will be recorded by a member of the local team on a Verbal Informed Consent Form during an informed consent video/telephone call and a copy sent to the participant.

### Allocation

After consent, participants will be randomised to usual care, usual care and independent exercise or usual care and supervised exercise on a 1:1:1 basis using a validated computer randomisation programme managed through a secure web-based service by the Oxford Clinical Trials Research Unit, with a minimisation algorithm to ensure balanced allocation across the three treatment groups, stratified by centre and initial fracture management (surgical vs. non-surgical). The first few participants will be randomised using simple randomisation to seed the minimisation algorithm and a probabilistic element will be introduced to the algorithm to ensure unpredictability of intervention allocation. On randomisation of a participant, the central trial office, main site contact and local study team will be notified via an automated email.

### Blinding

It will not be possible to blind the study participants or those delivering the interventions. The local research team reviewing hospital records and the trial statistician will also not be blind to the treatment allocation. The majority of outcome measures are patient-reported and collected electronically or via post, so clinicians involved in the care of patients will not be involved in outcome data collection within the trial. The research team member contacting the participants to offer support with remote hand strength measurements at 6 months after randomisation will be blinded to treatment allocation.

### Interventions

#### Usual care

On the day of cast or splint removal (usually 4 to 8 weeks after fracture), advice on self-management will be delivered by a surgeon, physiotherapist or occupational therapist in a fracture clinic, as per routine NHS clinical practice. Advice will include simple hand and wrist mobilisation exercises to restore flexibility and guidance on building up daily activity gradually. Participants may also receive a local advice leaflet, if routine practice at that hospital.

#### Independent exercise

Participants randomised to this treatment group will receive usual care and then a single physiotherapy or occupational therapy session (face-to-face or via videoconference or telephone) of up to 60 min duration no later than 3 weeks after the cast/splint removal. The purpose of this session will be to assess the participant and introduce the self-managed resistance exercise programme.

The WISE exercise programme utilises a range of progressive flexibility and resistance exercises based upon functional movements designed to promote recovery of the strength required for activities of daily living (e.g., chopping food, lifting, pushing and jar opening) and enable participants to progress their exercises after the initial set-up session with the therapist. Participants will be provided with resistance bands and putty to do the resistance exercises.

The behaviour change strategies will involve the participants identifying personal functional goals relevant to their wrist and hand function; making action plans as to where and when the home exercises will be performed; identifying barriers to exercise; and forming a contingency plan to manage difficulties in sticking to their exercises. Participants will be provided with a carefully designed, high-quality workbook that contains information on self-management, the WISE exercises, and goal planners and exercise diaries to complete. They will sign their goal planner (either on paper or electronically) during their first session with the therapist to confirm to themselves their intentions to doing exercises as there is evidence that this can facilitate engagement in an exercise programme [8].

Participants will also be given access to the WISE self-management website, if preferred over the workbook. The website content will mirror the workbook and also contain advice and exercise demonstration videos, written information and online goal planners and exercise adherence tracker via the exercise diary.

#### Supervised exercise

Participants randomised to this treatment group would receive usual care and access to the WISE exercise workbook and website and three individual therapy sessions (face-to-face or via videoconference or telephone) over 12 weeks. During the sessions, there will be opportunity for individualised feedback on progress of their rehabilitation. Therapists will focus on helping participants identify barriers to exercise and facilitate problem-solving.

#### Concurrent healthcare for all participants

Other aspects of the participant’s healthcare will be as per usual NHS local practice. In line with usual practice, participants that have difficulties with exercises will be supported over the phone/videoconference. We will carefully monitor the use of any additional contact required during the feasibility study. Participants will be able to access therapy services for post-fracture complications such as development of complex regional pain syndrome according to usual local routes of referral. The use of out of trial therapy will be captured in follow-up questionnaires.

### Primary feasibility outcomes

#### Patient engagement with the trial

The number of eligible participants who are screened, eligible and randomised will be collected to estimate the recruitment rate and proportion of patients willing to take part in the future trial.

#### Acceptability of the interventions

We will assess the acceptability of the interventions by therapist and participants’ adherence and their experiences with the WISE interventions.

Treating therapists’ adherence to the intervention protocol will be assessed by (1) number of therapy sessions provided by the therapists, (2) content of intervention sessions and (3) timing of sessions. For complete adherence, we expect one session to be provided and attended for the independent exercise group and three for the supervised exercise group. During each session, all core intervention components will need to be delivered. The first session will need to be delivered as soon as possible, at least within 3 weeks of cast/splint removal. Additionally, for supervised resistance exercise, all three sessions must be completed within 12 weeks from the first to last session.

In terms of participant adherence to exercise, we will record the proportion of participants who report performance of resistance exercises at home and use the exercise support materials (website and workbook).

As part of the feasibility evaluation, we will also conduct qualitative interviews with participants and a focus group with the treating therapists to understand their experience of the trial and trial interventions. Participant interviews will be undertaken via telephone/video call or face-to-face in order to understand the experience of (i) the intervention within the context of their daily life, (ii) what taking part in a randomised trial is like, and (iii) outcomes that are important to them. Up to 20 participants will be interviewed within 6 months of injury. Participants will be purposively sampled to ensure representation from each intervention group, including surgical and non-surgical management of their wrist. Patients who decline to take part in the randomised study will also be interviewed to explore the experience of (i) recovery from injury, thoughts and feelings about the intervention, what helped or hindered their recovery; (ii) thoughts and feelings about taking part in the trial and trial processes; and (iii) what they hope to achieve and challenges they have or may encounter.

Up to 15 therapists involved in delivering the trial interventions will be invited to participate in a face-to-face or online focus group to be held towards the end of the treatment phase to explore their experience of (i) delivery and fidelity of the interventions, (ii) what helped or hindered the patient’s ability to undertake the intervention and (iii) contextual factors that helped or hindered the trial. Interviews and the focus group will be digitally audio-recorded and transcribed verbatim. Analysis will be through coding sections of data, drawing codes with similar meanings together to form categories and themes. NVivo, a qualitative software package [9], will be used to manage the data.

#### Retention of participants in the trial

We will review the proportion of participants who complete and return their 3 and 6 month follow-up questionnaires. In addition, we will record the number of patients who complete and return grip strength measurements at 6 months.

### Progression criteria 

The feasibility objectives from our quantitative evaluation and their respective progression criteria are summarised in Table 1. Progression criteria to assess feasibility of a future definitive trial will be assessed using a traffic light system [10]. ‘Green’ indicates feasible with current procedures, ‘Amber’ indicates modification to one or more components of the protocol is required in order to proceed and ‘Red’ indicates a definitive trial would not be considered feasible.

**Table 1 Tab1:** Feasibility objectives and progression criteria

	Green (feasible)	Amber (modify)	Red (not feasible)
Feasibility objective 1: Patient engagement with the trial			
Recruitment acceptability	≥ 50% of eligible patients screened are consented and randomised	20–50%	< 20%
Recruitment rate	≥ 4 participants recruited per recruiting month per centre	1–3 per month per centre	< 1 per month per centre
Feasibility objective 2: Acceptability of the interventions			
Intervention adherence	> 75% of participants receive the allocated intervention sessions as per protocol	55–75%	< 55%
Feasibility objective 3: Retention of participants in the trial			
Proportion of randomised patients providing outcome data at 6 months follow-up	< 20% loss to follow-up at 6 months (including deaths and withdrawals)	20–30%	> 30%

### Secondary exploratory outcomes

We will also collect the following exploratory outcomes as part of this feasibility study to determine their viability for inclusion in a future definitive trial.Wrist pain and function: Wrist pain and function measurement using the Patient Reported Wrist Evaluation (PRWE) [11] recommended by the Core Outcome Measures in Effectiveness Trials (COMET) guidance [12] for distal radius fractures will be followed. PRWE is a 15 item patient-reported questionnaire that assesses pain and functional difficulties in activities of daily living resulting from injuries affecting wrist joint area. The pain subscale has 5 items (each rated 0 = no pain to 10 = worst pain) and the function subscale has 10 items (each rated 0 = no difficulty to 10 = unable to do). Total score ranges from 0 to 100, higher scores indicate worse wrist pain and function.Upper extremity physical function: Patient Reported Outcome Measurement Information System (PROMIS) [13] Physical Function (Upper Extremity) questionnaires will be administered electronically. They are a Computer Adaptive Test, which are dynamic tests based on Item Response Theory. A mathematical model adapts the sequential questions asked based on a participants’ previous response. A tailored set of questions is therefore asked from a large item pool. PROMIS instruments are scored from 0 to 100 with 50 points representing the mean score for the US general population, higher scores indicate better function. This questionnaire has been found to be valid in the context of upper limb fractures in the UK [14, 15]. Participants with no Internet access will be able to complete a paper-based version of the questionnaire (PROMIS Upper Extremity Short Form, 7a).Self-efficacy: The Self-Efficacy for Exercise Scale [16] is a 9-item questionnaire (total scores range from 0 to 90, higher scores indicate higher self-efficacy for exercise) that will be used to assess participants’ confidence in their ability to do exercise.Exercise adherence: Participants will be asked to indicate how many times in the preceding week they have done specific exercises for their injured hand and upper extremity, to assess engagement with the advised exercises after wrist fracture.Quality of life: The EuroQol 5 Dimensions (EQ-5D-5L) is a validated, generalised and standardised instrument comprising a visual analogue scale (VAS) measuring self-rated health and a health status instrument, consisting of a five-level response (no problems, some problems, moderate problems, severe problems and unable) for five domains related to daily activities: (i) mobility, (ii) self-care, (iii) usual activities, (iv) pain and discomfort and (v) anxiety and depression [17]. Responses to the health status classification system are converted into an overall score using a published utility algorithm for the UK population. The EQ-5D health status scale ranges from negative scores − 0.594 [reflective of a patient’s quality of life being worse than death], 0 [death], to 1 [perfect health]. A respondent’s EQ-VAS gives self-rated health on a scale where the endpoints are labelled ‘best imaginable health state’ (100) and ‘worst imaginable health state’ (0).Health resource use: A bespoke health resource use questionnaire will be used to assess the number of primary and secondary care consultations, additional therapy appointments, further wrist x-rays and scans, surgery and over-the-counter pain medication prescribed, out-of-pocket expenses and work absence.Adverse events: Adverse events related to the randomised interventions will be recorded.

A serious AE (SAE) is any unexpected untoward medical occurrence relating to the trial interventions resulting in death, is life-threatening, requires inpatient hospitalisation or prolongation of existing hospitalisation or persistent or significant disability/incapacity. In the event of any SAE, the Clinical Trials Unit standard operating procedures will apply.

Foreseeable SAEs and adverse events not defined as serious that are related to the interventions will be recorded by participants or site staff but will not need to be reported immediately. These events will be recorded on patient-reported questionnaires or by the site investigators in the ‘Complications’ case report form if they become aware of such an event.

Foreseeable adverse events include:Increases in pain lasting more than 1 weekTreatment-related exacerbations of other medical conditions that do not meet the definition of serious (for example angina after exertion)Development of Complex Regional Pain SyndromeSurgery to the injured wrist (unless an adverse event directly related to the exercise intervention, in which case this would be an SAE)

Safety reporting will begin from the point of randomisation and end when the participant has reached their final main follow-up time point, at 6 months post-randomisation.Muscle strength of the upper limb: Force produced during cylindrical grip will be measured using a commercially available hand-held dynamometer in a sitting position, as recommended by the American Society for Hand Therapists [18, 19]. Three attempts will be recorded for each hand alternatively, starting from the uninjured side on two consecutive days. Participants are asked to wait a minimum of 30 s between recording measurements. The best grip score for each hand will be recorded.Balance and mobility: Participants will be asked Likert type questions on balance and mobility to assess how this is progressing since their injury.

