#### Three- and six-month follow-up

Participants will receive an electronic/paper invite to complete questionnaires which include the PRWE, PROMIS, EQ-5D-5L, self-efficacy to exercise, current balance and mobility status, exercise frequency, resource use and adverse events. Reminders will be sent by email, post and/or text message (according to the participant’s preference); if questionnaires are not completed, these will be followed by a phone call from the central team if required.

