### Statistical methods

Analysis methods will be guided by the demonstration of feasibility. If feasibility is not demonstrated and a definitive trial is not conducted, then outcome data for the ITT population will be analysed and reported for each randomised group. In this case the feasibility outcomes and baseline characteristics will be reported using descriptive statistics. Mean and standard deviation or median and interquartile range will be used for continuous variables and counts and percentages will be used for any binary or categorical variables. Missing data will be minimised by careful data management. No comparative statistical testing will be undertaken as this is a feasibility study and is not powered for this purpose.

If feasibility is demonstrated, outcome data will not be analysed by group as we would take participants and their data from the feasibility and pilot study forward into the definitive trial.

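### The SAE definition requires an event to be unexpected and related, which leaves foreseeable SAEs undefined, and the rules on which adverse events are recorded are inconsistent and may depend on unblinded attribution

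*Protocol article*

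**What the plan says.** All the safety definitions stand in the Protocol article under Secondary exploratory outcomes.

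- **Outcome list.** "Adverse events related to the randomised interventions will be recorded".
- **SAE definition.** "A serious AE (SAE) is any unexpected untoward medical occurrence relating to the trial interventions resulting in death", followed by the other seriousness outcomes (threat to life, admission or prolonged admission, lasting disability). For any SAE, the trials unit's standard operating procedures apply.
- **Recording rule.** "Foreseeable SAEs and adverse events not defined as serious that are related to the interventions will be recorded by participants or site staff", without immediate reporting. On the route: "These events will be recorded on patient-reported questionnaires or by the site investigators", the latter on a complications form and only if the site learns of the event.
- **Foreseeable list.** It has four items: pain increases beyond a week; treatment-related, non-serious worsening of other conditions; complex regional pain syndrome; and surgery to the injured wrist. Surgery directly related to the exercise intervention is carved out and called an SAE.

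Three other sections bear on the point. Blinding says: "It will not be possible to blind the study participants or those delivering the interventions", and adds that the local research team is not blind either. The three- and six-month questionnaires include "current balance and mobility status, exercise frequency, resource use and adverse events". Statistical methods says that, if feasibility is shown, "outcome data will not be analysed by group", because participants and their data would pass into the definitive trial.

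**The concern.** Seriousness, relatedness and expectedness are three separate judgements. Seriousness describes the outcome of an event and can be applied in the same way in every arm. Relatedness and expectedness depend on what treatment the participant had and on who is judging. When all three sit in one definition, a serious event that is unrelated or foreseeable is not an SAE under the article's own words, and the article does not say clearly how such an event is recorded.

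Two things are at stake. The first is operational: a site must be able to tell which reporting route an event takes. The second is statistical: if an event is recorded only when someone links it to the intervention, and those people know the allocation, the recorded counts mix the true event rate with the tendency to attribute. Events left unrecorded for that reason may not be recoverable once the data sit inside a comparative trial.

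**Working it through.** The plan gives no figure on this point, so the check sets the rules side by side.

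**1. SAE definition against the recording rule.** Under the definition, an SAE is serious, related and unexpected. A foreseeable SAE would have to be both unexpected and foreseeable, so the class is empty. The recording rule nevertheless relieves that class of immediate reporting, while the SAE paragraph sends every SAE to the unit's procedures.

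**2. The surgery item.** Wrist surgery is named as foreseeable. Surgery directly related to the exercise intervention is then called an SAE, which the definition requires to be unexpected. One can read the exception as taking such surgery off the foreseeable list, which makes the item coherent, but the text does not say so. The Interventions section lists usual care among the trial's interventions, and that care includes simple mobilisation exercises. The phrase used in the surgery item, however, most naturally means the structured exercise programme. On that reading the same operation can be an SAE in two arms and never in the third.

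**3. Scope of recording.**

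| Source | Relatedness required? |
|---|---|
| Outcome list | Yes |
| Recording rule | Yes |
| List: worsening of other conditions | Yes, stated in the item |
| List: prolonged pain | Not stated |
| List: complex regional pain syndrome | Not stated |
| List: wrist surgery | Stays on the list when not directly related |

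If the general rule governs every listed item, the words in the second list item are redundant and the surgery item sits oddly. If it does not, the outcome list is too narrow. The article supports either reading.

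**4. Who attributes, and who becomes aware.** The article names participants and site staff as recorders. It does not say who judges causality. Participants, those delivering treatment and the local research team all know the allocation. The site form depends on awareness, and planned trial therapy sessions beyond usual care number none, one and three in the three arms.

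**5. What this does to counts.** Let each arm have n participants, the same true event rate r, and a probability a that an event is called related and so recorded. Expected recorded events are n × r × a. With n and r equal, the ratio between two arms is a₁/a₂: equal attribution gives no difference, and unequal attribution gives a difference with no true effect behind it. The article gives neither r nor a. So the mechanism follows from the rule, but its size does not.

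**The case against.** The strongest reply is that the damage is small. The article condenses a fuller protocol and defers SAE handling to unit procedures that are not shown; the causality assessor and the form fields may well be there. That stands, and their absence is not criticised here. It does not remove the contradiction, because the definition printed in the article decides what enters those procedures.

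Several stronger conclusions are tempting but not supported.

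- *Harms cannot be compared fairly between arms.* The follow-up questionnaires, not described as arm-specific, ask about adverse events and resource use, and the resource-use questionnaire covers surgery and secondary care consultations. This is a partial parallel source. No comparative testing is planned in this trial.
- *The safety evidence behind progression is uninterpretable.* Table 1 has four criteria, on recruitment acceptability, recruitment rate, adherence and retention. None concerns safety.
- *Complex regional pain syndrome is classed differently by arm.* It is listed with no arm or relatedness condition.
- *The no-by-group rule suppresses harms.* By-group analysis is deferred to the definitive trial. The section on early discontinuation and withdrawal mentions a safety analysis separately from the main one, so it is not established that the rule covers adverse events. It is merely unclear.
- *A worked count shows the bias.* With 72/3 = 24 per arm, one can assume two operations in each arm and call all those in the exercise arms related, giving 2, 2 and 0. Both the rate and the attribution are assumed, so this is not evidence.

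**Conclusion.** The concern holds in a limited form. The SAE definition and the rule for foreseeable SAEs contradict each other. The surgery item is tied to the exercise intervention and, on its natural reading, can produce an SAE only in the exercise arms. The rules on which adverse events are recorded are inconsistent, and recording may depend on attribution by people who know the allocation.

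No size can be attached to any resulting bias, which may be nil. The consequence lies chiefly in the data that may be carried into the definitive trial, where arms will be compared. It does not lie in this trial's progression decision. The verdict rests on two assumptions: that the phrase in the surgery item means the structured programme, and that the full protocol does not replace these definitions. The change is worth making because it is cheap.

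**What to change.** - Define seriousness by outcome only, in the same words for all three arms.
- Record relatedness and expectedness as two separate fields.
- Record the listed complications and all serious events in every arm, regardless of attribution, and align the outcome list and the recording rule with this.
- Reconcile the foreseeable SAE wording and the surgery item with the new definition and with the immediate-reporting rule, so that each event has one reporting route.
- State in Statistical methods whether the no-by-group rule applies to adverse events.

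The cost is protocol wording, two form fields (unless the complications form, which is not shown, already has them) and slightly more recording at sites. Recruitment was under way when the article was submitted, so events already recorded would need to be classified under the new fields.
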